## Abstract

**Background:**

Adjuvant endocrine therapy (AET) is an oral treatment prescribed for 5 to 10 years to women with hormone-sensitive breast cancer. Despite the benefits of AET for reducing breast cancer recurrence, suboptimal adherence is common. Community pharmacists can play a role in supporting women with this treatment, given their frequent encounters with patients, access to refill information, and expertise in managing side effects. The goal of this pilot study is to assess the acceptability and feasibility of implementation, and preliminary effects of the PACHA program, a community pharmacy-based program designed to support women who are prescribed AET. Another goal is to assess the feasibility of a large-scale randomized controlled trial (RCT).

**Methods:**

This is a pilot cluster-RCT using mixed-methods. A cluster consists of a pharmacy, its pharmacists, and its patients with an AET prescription in the last 30 months. Pharmacies will be recruited through targeted advertisement. Participating pharmacies will be randomized 1:1 to two groups (*n* = 33 pharmacies per group). In the first group (control), pharmacists will provide usual services to women. In the second group (intervention), pharmacists will complete web-based training and perform consultations using a standardized guide based on motivational interviewing principles and evidence-based online strategy sheets to cope with AET side effects. Women in the intervention group will have access to a website featuring video modules on AET, strategies for managing side effects, testimonials from women who have had an AET, and a list of resources. Acceptability and feasibility indicators, as well as psychosocial factors expected to influence AET adherence and treatment experience, will be collected at baseline, during, and at the end of the 6-month follow-up using online questionnaires, study data logs, and pharmacy claim records. Semi-structured interviews will be conducted to explore participants’ experiences with the program.

**Discussion:**

Results will help to refine the program and, if the results support this, to design a full-scale cluster-RCT to assess the program’s effect on 5-year adherence and costs. If effective, this program could fill a gap in breast cancer supportive care and contribute to reducing cancer burden by improving survivorship experience and survival.

**Trial registration:**

This trial has been approved by the Research Ethics Board of the CHU de Québec-Université Laval (MP-20–2023-6625) and registered at Clinicaltrials.gov (NCT05887102) on 2023–05-24, https://classic.clinicaltrials.gov/ct2/show/NCT05887102, prior to beginning the study. Protocol version 1 is dated as 2022–12-12.

## Background

Breast cancer is the most common cancer in women worldwide [1]. Adjuvant endocrine therapy (AET) (i.e., tamoxifen or aromatase inhibitors) is an oral medication prescribed to women with hormone-sensitive breast cancer (60% to 75% of cases [2, 3]) to reduce recurrence and mortality risks [4]. AET must be taken daily for 5 to 10 years after other treatments, such as surgery, radiotherapy, and chemotherapy [5, 6]. Five years of tamoxifen reduces recurrence rates during the first 5 years by 47% and breast cancer mortality by 30% 15 years after diagnosis [4]. The efficacy of aromatase inhibitors is even greater in post-menopausal women [7].

AET can be challenging for patients who have to self-manage their treatment [8, 9]. Despite the widely recognized clinical benefits of AET, suboptimal AET adherence (i.e., non-persistence or sub-optimal implementation) is common [10–13]. A meta-analysis estimated that 47% and 31% of women prescribed tamoxifen and aromatase inhibitors, respectively, did not persist with their AET for 5 years [13]. Another systematic review indicated that 28% to 59% of patients collected less than 80% of their prescribed doses [10]. Non-adherence has been found to be associated with an increased risk of breast cancer recurrence and mortality [14, 15] and higher costs for the healthcare system [16]. Several factors must be considered to improve AET adherence, such as the management of AET side effects (e.g., hot flashes, musculoskeletal pain, and insomnia), the provision of sufficient information on AET and the availability of supportive patient-provider relationships and communication [17–21].

The development and evaluation of innovative approaches for enhancing AET adherence are needed to attain the full benefits of this treatment. A recent meta-analysis reported that existing AET adherence interventions provided positive but small effects [22]. However, none of these interventions tested the potential impact of community pharmacists on AET adherence. Nevertheless, community pharmacists are pharmacotherapy experts and can play a key role in enhancing AET adherence. They frequently interact with patients, have access to medication data to detect non-adherence, and have the expertise to suggest and implement strategies to optimize medication use and overcome side effects. This is especially true in several jurisdictions where the role of pharmacists has evolved over the past few decades from drug distribution to performing more clinical interventions [23].

To optimize AET adherence, we co-designed the PACHA program *(programme en Pharmacie pour l’ACcompagnement des femmes ayant de l’Hormonothérapie Adjuvante—*in English, *Pharmacy program for supporting women undergoing adjuvant endocrine therapy)*. PACHA is, to our knowledge, the first community pharmacy-based intervention specifically aimed at enhancing AET adherence among women with non-metastatic breast cancer [24]. As a first step, we designed a pilot study to determine if involving community pharmacists to support breast cancer survivors with AET is acceptable, feasible, and promising. More specifically, this pilot study evaluates the program’s (1) acceptability from the pharmacist’s and patient’s perspective, (2) feasibility of implementation, (3) preliminary effects on factors expected to influence AET adherence according to our conceptual model (intention to adhere to AET, AET knowledge, attitude, perceived social support, perceived behavioral control, anticipated regret, coping planning, and fear of recurrence), and (4) feasibility and required sample size for a large-scale randomized controlled trial (RCT).

## Methods

### Study design and setting

This is a pilot cluster-RCT with a 6-month follow-up, using mixed methods (quantitative and qualitative) and recruiting in the province of Québec, Canada. Following the Medical Research Council framework for complex interventions [25], the PACHA program and study procedures will be pilot-tested to guide decisions regarding the development of a large-scale, cluster-RCT assessing the effects of the program on 5-year AET adherence and healthcare system costs. The need for a pilot study lies in the novelty of the program and the anticipated challenges related to implementing interventions and conducting a RCT in community pharmacies [26]. A cluster is defined as a community pharmacy, its pharmacists, and its recruited patients. Cluster randomization is necessary to prevent between-group contamination (i.e., pharmacists in the control group exposed to PACHA training and tools). The PACHA program will be compared to usual community pharmacy practice. Each cluster will be followed for 6 months after their inclusion in the study (randomization). See Table 1 for the study timetable. This trial has been approved by the Research Ethics Board of the CHU de Québec-Université Laval (MP-20–2023-6625) and registered at Clinicaltrials.gov (NCT05887102) on 2023–05–24, prior to beginning the study. The study is presented according to the SPIRIT recommendations [27].

**Table 1 Tab1:**
[figure not shown]
Study timetable according to SPIRIT guidelines for presenting the study’s phases

### Intervention

Given the complexity of medication-taking behaviors, we opted for an adaptation of the Behavioral Model for Medication Adherence [28, 29] to guide the development and evaluation of the PACHA program [24] (see Fig. 1). This model is based on the Theory of Planned Behavior, one of the most cited and influential theoretical models for predicting behaviors [30, 31]. It was adapted for AET adherence and empirically validated in a qualitative study we conducted among 43 patients [32]. This model depicts the factors expected to influence AET adherence. In this model, AET adherence is influenced by the patient’s *behavioral intention*, i.e., the degree to which the patient intends to take the AET as prescribed. Numerous *barriers* (e.g., side effects) can hinder the translation of this intention into AET adherence. Conversely, *facilitators* (e.g., establishment of a routine) can help translate intention into AET adherence. *Intention* is, in turn, influenced by *AET knowledge, attitude*, *perceived social support*, and *perceived behavioral control*. *Attitude* refers to balancing the perceived advantages and disadvantages of adhering to AET. *Perceived social support* refers to the extent to which patients perceive that significant others and healthcare professionals support them in adhering to AET. *Perceived behavioral control* refers to whether the patients feel able to face barriers. In our previous research [32], anticipated regret (i.e., the feeling one would experience if a behavior was not adopted [33]), coping planning (i.e., strategies one would adopt to overcome potential barriers to action [34]), and fear of recurrence were also found to be important factors influencing AET adherence and were added to the model. In addition to intention, perceived behavioral control is also hypothesized to directly influence AET adherence.

**Fig. 1 Fig1:**
[figure not shown]
Conceptual model guiding the intervention development and evaluation adapted from the Behavioral Model for Medication Adherence

The PACHA program was co-designed by a planning group (*n* = 11) of researchers (expertise in medication adherence, health interventions, breast cancer), a hospital pharmacist specializing in oncology, patients who were prescribed an AET, and community pharmacists. We followed the six steps of Intervention Mapping, an approach guiding the development, implementation, and evaluation of complex behavioral interventions in health promotion [35]. In *Step 1*, a conceptual model was drawn up based on a literature review on AET adherence [10, 12, 17, 36–39] and a qualitative study conducted by our team [32]. In *Step 2*, program objectives were formulated based on this conceptual model. The behavioral objective of the intervention is that “Each patient with a new prescription has an optimal use of AET”. Six different performance objectives were deemed essential to achieve this behavioral objective. Change objectives were defined at the intersection of factors influencing AET adherence arising from the conceptual model and performance objectives. In *Step 3*, the theoretical methods and practical applications to fulfil these objectives were selected. Principles of motivational interviewing (MI), a collaborative conversation style to reinforce a person’s motivation and commitment to change [40], were chosen and adapted for the pharmacist’s intervention. MI has a positive effect on drug adherence for chronic diseases [41, 42]. In community pharmacy practice, the potential of MI lies in its ability to be effectively implemented within the typically brief consultation time frames [43] and the fact that it is increasingly being taught in pharmacy faculties [44, 45]. In *Step 4*, the program sequence and tools were developed. In *Step 5*, an implementation plan was developed by creating a second matrix of change objectives. In *Step 6*, the evaluation plan and the pilot study were designed. The development of the program was guided by the idea that it should be low-cost, aligned with provincial pharmacy practice standards, brief and easy to integrate into pharmacy operations, and tailored to meet patients’ specific needs. Results of this Intervention Mapping process were published [24].

PACHA includes components for both the pharmacists and the patients. For the pharmacists, components are as follows: (1) web-based training eligible for continuing education credits about AET and AET consultations based on MI; and (2) standardized tools to guide their AET consultations (consultation guide based on MI principles and a series of evidence-based sheets of non-pharmacological and pharmacological strategies for coping with AET side effects). For the patients, it includes (1) web-based video modules about AET; (2) self-management strategies for coping with specific AET side effects; (3) testimonials from patients using an AET; and (4) a detailed list of resources for breast cancer survivors (e.g., national and provincial breast cancer societies or foundation website links and toll-free helplines). Table 2 provides a detailed description of the intervention (i.e., PACHA program) compared to usual care (i.e., usual care (UC)).

**Table 2 Tab2:** Description of the PACHA program group and the usual care group

**PACHA program group**	**Usual care group**
**For the pharmacists : ** **An 85-minute web-based training **comprising three main sections: 1) a review of AET pharmacotherapy; 2) information on AET consultation based on the principles of motivational interviewing with video simulations; and 3) access to materials geared to participating patients (video modules about AET, self-management strategies for coping with specific AET side effects and list of resources). The training can be completed in one or several sessions in the weeks after randomization. Pharmacists who complete the training can request continuing education credits from their regulatory licensing body, the *Ordre des pharmaciens du Québec *(OPQ). **Standardized consultation guide **based on motivational interviewing principles to guide AET telephone consultations.This standardized consultation guide outlines the key steps that the pharmacist must cover during the AET consultation and follows the usual sequence of consultation in pharmacy. This consultation guide is to be used in the first month and 4 months after randomization, or more frequently according to the needs. **Evidence-based web sheets **describing (non)pharmacological strategies to cope with side effects (e.g. hot flashes) and other AET-related concerns (e.g. sexuality). **For the patients : ** **Web-based video modules **to inform patients about AET.These video modules cover how to and why take tamoxifen or an aromatase inhibitor, the possible side effects and strategies to cope with these side effects and, finally, medication intake and daily activities (e.g. diet). **Evidence-based web sheets **describing (non)pharmacological strategies to cope with side effects (e.g. hot flashes) and other AET-related concerns (e.g. sexuality) in a version adapted for the patient. **Testimonies** of patients who had breast cancer and an AET. **List of resources** available to patients who needs help in coping with side effects and other AET-related concerns.	**For the pharmacists and patients: ** Pharmacists and patients in the usual care (UC) group will not have access to the program during the study and will continue to provide/receive their usual services (e.g. AET information, suggestions to deal with side effects). Pharmacists will be offered the web-based training at the end of the study and patients will be provided with access to the website.

#### PACHA program pre-testing

PACHA program components were pre-tested in two steps. *Step 1*: community pharmacists (*n* = 7) received online access to the intervention components. Appropriateness, completeness, acceptability, and feasibility were assessed through semi-structured interviews. Participants reported an overall high appreciation of the web-based training and judged that the intervention tools were well-structured, relevant, and presented in an accessible manner. The main areas of improvement mentioned were (1) offering further explanation about how MI principles could enhance pharmacists’ interventions; (2) showing the different tools and their use in greater detail in the video simulations; and (3) making the program delivery more flexible when the pharmacy is very busy (e.g., making an appointment with the patient or doing consultations by telephone; strategies that are already used in current pharmacy practice). *Step 2:* we conducted a study using simulated consultations with community pharmacists (*n* = 3) who completed the web-based training and patients on an AET (*n* = 7). Patients received the program at the Université Laval’s mock pharmacy, which is used to train pharmacy students. An individual semi-structured interview on the experience with providing/receiving the program was conducted with participating pharmacists and patients. The program components were refined based on feedback and the post-pandemic context of pharmacy practice. Indeed, the PACHA program consultations were initially conceived to be offered face-to-face [24]. However, due to changes in pharmacy practice following the COVID-19 pandemic, and after consulting with community pharmacists, some program components were modified to be delivered online or via telephone, instead of face-to-face.

### Eligibility criteria

*Community pharmacies* are eligible to participate if (1) at least one pharmacist agrees to take charge of the project in their pharmacy and provides consent; and (2) at least one patient has initiated AET in the last 30 months in the pharmacy and provides consent. *Patients* are eligible if they (1) are a woman; (2) ≥ 18 years; (3) were diagnosed with a first non-metastatic, hormone-sensitive breast cancer (endocrine therapy may also be prescribed to patients with metastatic disease, but in this case, the patient takes the drug to treat active cancer and so, adherence issues may differ); (4) received an AET prescription for the first time in the last 30 months; (5) are fluent in French (78% of the Quebec population) [46]; (6) have internet access; and (7) provide consent. Excluded are patients who live in a residential facility where AET is not self-managed.

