**Feasibility of a large-scale cluster randomized controlled trial**							
Recruitment rates and channels	- Recruitment algorithm	- Descriptive statistics		X	X	X	X
Reasons for refusal	- Study data logs	- Descriptive statistics		X		X	X
Randomization process	- Recruitment algorithm	- Descriptive statistics		X		X	X
Cluster size	- Study data logs	- Descriptive statistics		X			
Frequency of contact between participants and research team	- Study data logs	- Descriptive statistics		X		X	X

Outcomes related to the *preliminary effects on factors expected to influence AET adherence*, such as intention to adhere to AET, AET knowledge, attitude, perceived social support, behavioral control, anticipated regret, and coping planning, will be assessed by questionnaire. We developed this questionnaire following the recommendations of the developers of the Theory of Planned Behavior [50] and our previous qualitative study [32]. The questionnaire was validated in a test–retest study among 67 patients with an AET, and each scale presented very good psychometric properties (Cronbach’s alphas and intraclass correlation coefficients ≥ 0.70). Other important measures will be collected using validated measures in their official French versions: side effects (Functional Assessment of Cancer Therapy—Endocrine Symptoms (FACT-ES) [51]), fear of cancer recurrence (Fear of Cancer Recurrence Inventory [52]), beliefs about medication (Beliefs about Medicine Questionnaire – adjuvant endocrine therapy [53]), patient-pharmacist relationship (Consultation and Relational Empathy (CARE) measure [54, 55]), and quality of life (Functional Assessment of Cancer Therapy – Breast (FACT-B) [56]).

We will appraise the program's preliminary effects on *AET **adherence* (AET initiation, implementation, and persistence) [57] through self-reported measures (i.e., using questions developed by our team and the Medication Adherence Report Scale (MARS) [58]) and calculate it using pharmacy claims for the 6-month follow-up. Data on drug identifier, delivery date, prescribed regimen, and duration of supply will be used to calculate AET initiation, non-persistence, and implementation for any AET, not just the one initially prescribed. Non-persistence will be defined as not claiming an AET at the expected date, allowing for a 90-day permissible gap. Implementation will be defined through the proportion of days covered (PDC) by any AET divided by the number of days of follow-up [59].

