### Analyses

Descriptive statistics for pharmacies, pharmacists, and patients in the PACHA program and UC group will be reported and compared. Acceptability and feasibility indicators such as recruitment and retention rates will be evaluated using percentages or means and 95% CI [69]. To explore preliminary effects on factors expected to influence AET adherence, generalized estimating equation (GEE) regression models will be used to compare patterns of change in scores of factors influencing AET adherence between the two groups over time. The group-by-time interaction *p*-value will be used to test the differences between the two groups. Effect sizes will be estimated using Cohen’s *d*. The required sample size for a large-scale cluster RCT will be estimated using the PDC, its variability, and ICC. Missing data will be handled using various strategies according to the variables. For instance, mean score imputation (if at least half of the items are completed) will be applied to scales, while listwise deletion will be used for other variables [70]. For qualitative data, thematic analysis of the interviews will be conducted [71, 72]. Since this is a pilot study, analyses will be performed at the end of the study, and no subgroup analyses will be performed.

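### Current AET use is not an entry condition, and the adherence outcomes and main-trial PDC inputs do not separate women who had already stopped before randomization

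*Protocol article*

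**What the plan says.** The protocol article's Eligibility criteria section numbers seven conditions for patients. The only one concerning the drug is that the woman "received an AET prescription for the first time in the last 30 months". One exclusion follows: "Excluded are patients who live in a residential facility where AET is not self-managed". The abstract describes a cluster's patients in similar terms: "its patients with an AET prescription in the last 30 months". The Recruitment section adds no check of current use.

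Study design and setting starts the 6-month follow-up at randomization. The adherence paragraph of the Outcomes section, after Table 3, defines two claims-based measures over that period:

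- "Implementation will be defined through the proportion of days covered (PDC) by any AET divided by the number of days of follow-up".
- "Non-persistence will be defined as not claiming an AET at the expected date, allowing for a 90-day permissible gap".

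Table 3 marks adherence at the end of the study only. The Analyses section then says: "The required sample size for a large-scale cluster RCT will be estimated using the PDC, its variability, and ICC". Estimating that sample size is part of the fourth objective listed in the Background, which also reports from a meta-analysis that "47% and 31% of women prescribed tamoxifen and aromatase inhibitors, respectively, did not persist with their AET for 5 years".

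**The concern.** A woman first prescribed AET 24 months ago who stopped 10 months ago meets every listed criterion. Her follow-up starts with no supply in hand, so her PDC is 0 unless she restarts. The non-persistence rule needs an expected claim date. Either she has none after randomization, or her last expected date and the 90-day allowance both lie before it. In the second case an event from before the trial is recorded as a follow-up outcome.

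Two things are at stake. Non-persistence would mix earlier stopping with stopping during the program period. And the PDC spread handed to the main trial would come from two groups, one clustered near 0 and one of current users, with nothing in the stated plan to show how much of the spread each contributes. The Background's own discontinuation figures make such women foreseeable in a 30-month window.

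**Working it through.** **1. The plan's own figures.** The Sample size section gives 66 patients per group, clusters of mean size 2, ICC 0.02, baseline-to-follow-up correlation 0.5, α = 0.05 (taken as two-sided) and power 0.80 for d = 0.50. The design effect is 1 + (2 − 1) × 0.02 = 1.02, and the SD of change is √(2(1 − 0.5)) = 1. Power comes to 0.812 and the smallest detectable d to 0.493, so the statement reproduces. The Wald intervals reproduce to within about 0.1 percentage point. None of these figures uses PDC. The article states no PDC mean, SD or main-trial size, so there is nothing further to reproduce.

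**2. Share already stopped (illustrative).** Inputs: 31% and 47% five-year non-persistence, from the Background. Assumptions: constant hazard, and time since first prescription spread evenly over 0 to 30 months.

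- Hazard per month h = −ln(1 − F)/60, which is 0.00618 for F = 0.31 and 0.01058 for F = 0.47.
- Mean share stopped q = 1 − (1 − e^(−30h))/(30h), which is 0.087 and 0.143.
- Out of 132 women, that is about 12 to 19.

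Stopped women may be approached or consent less often, so 3% and 5% are also shown.

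**3. PDC variance.** If a share q has PDC 0 and the rest have mean m and SD s, then

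Var = (1 − q)s² + q(1 − q)m².

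The values of m and s are assumed.

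| Share stopped q | m = 0.90, s = 0.15: SD (variance ratio to s²) | m = 0.80, s = 0.25: SD (variance ratio to s²) |
|---|---|---|
| 3% | 0.213 (2.0) | 0.282 (1.3) |
| 5% | 0.245 (2.7) | 0.300 (1.4) |
| 8.7% | 0.292 (3.8) | 0.329 (1.7) |
| 14.3% | 0.344 (5.3) | 0.363 (2.1) |

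Worked example, q = 0.143, m = 0.90, s = 0.15: 0.857 × 0.0225 + 0.143 × 0.857 × 0.81 = 0.0193 + 0.0993 = 0.1186. Divided by 0.0225, this is 5.3.

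**4. Direction.** Var − s² = q[(1 − q)m² − s²], so the pooled variance exceeds that of current users whenever (1 − q)m² > s². Every row above satisfies this.

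**5. Consequence for sizing.** For a fixed difference, the sample size moves in proportion to the variance. Assume a PDC difference of 0.05, 80% power, two-sided α 0.05, and no design effect. With m = 0.90 and s = 0.15, current users alone need 142 per arm, and a population with 5% stopped needs 376. The wrong variance can mislead in either direction: the pooled figure oversizes a trial of current users, and the current-user figure undersizes a trial that admits women who have stopped.

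**The case against.** The strongest reply is that the main trial's eligibility is not stated. If it keeps the pilot's criteria, the pooled variance is the right input, and sizing on current users alone would leave that trial too small. This stands. A reader might infer that the pilot necessarily inflates the main-trial sample size, and the article does not support that. Its five-year adherence aim and a behavioral objective framed around new prescriptions suggest a different population but do not establish one.

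A reader might also infer that these women's adherence is settled before randomization. That goes too far. PDC counts any AET, a woman may restart, and a program built on motivational interviewing may prompt her to. Admitting her may be a deliberate choice.

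The multipliers rest on an assumed PDC mean, SD and share stopped, and the table shows how far they move. The upper end is not an estimate. Pharmacy staff make first contact and may approach mainly current users.

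Consequences within the pilot are limited. Adherence is summarized descriptively, no progression criterion uses PDC or persistence, and randomization balances earlier stoppers in expectation.

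Finally, status at randomization might be treated as detail for the full protocol or SAP. The article does not rule out identifying it: it collects medical characteristics at baseline, and delivery dates and days of supply from claims. But it does state the eligibility list, the outcome rules and the inputs for sizing. Followed as written, they pool stopping before randomization into non-persistence and into the PDC variance.

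**Conclusion.** The point holds as a gap between who may enter and how adherence is counted. Women who stopped before randomization are eligible; their PDC is near 0 unless they restart; and the non-persistence rule does not fit them. The PDC spread intended for the main trial may therefore describe a mixed population without showing it. Under the assumptions above, the pooled variance is about 1.3 to 5.3 times that of current users. The range is illustrative, since neither the number of such women nor any PDC mean or SD is given. Whether that variance is too large for the main trial depends on eligibility the article does not state. The pilot's power, confidence intervals and progression criteria do not change.

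**What to change.** - Leave eligibility unchanged.
- Classify each woman as having or not having AET supply at randomization, from the last dispensing date and days of supply or from one baseline item.
- Limit non-persistence to women on AET at randomization. For those already stopped, report resumption of AET.
- Report PDC mean, SD and ICC both overall and among women on AET at randomization, and size the main trial with the set that matches its eligibility.

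All women stay in the acceptability and psychosocial analyses. The cost is one baseline item or a lookup in dispensing records, a sentence or two in Outcomes and Analyses, a slightly smaller denominator for non-persistence, and a little extra analysis.
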